### 3.1 Outcome Measures

- Baseline levels of variation in the work-up, recognition, and management of medication non-adherence and/or DDI in patients with more than one chronic cardiometabolic conditions and associated polypharmacy among all participants.
- Pre- and post-difference in the overall and the work-up, recognition and management quality scores between control providers using standard of care diagnostic tools and intervention providers with access to CDMT results.
- Differences in evidence-based decisions, particularly prescribing decisions, made by intervention providers and control providers, while controlling for provider and practice characteristics, between rounds 1 and 2.
- Distinguishing between medication non-adherence, DDI, and full compliance with suboptimal medication treatment (inadequate dosing vs. ineffective medication).
- Difference in expected cost of care between control and intervention providers (Cost will be calculated by measuring differential rates of medical interventions/levels of care selected by each arm, and multiplying by Medicare reimbursement rates for these interventions, and/or by modeling the incidence of expected complications and calculating associated costs per above).
- Difference in the above cost and clinical quality metrics and cost measures by three different use case types.

## 4. ELIGIBILITY CRITERIA

### a. Description of subjects

Practicing providers will be the study subjects with the following eligibility criteria.

#### Inclusion Criteria

Subjects must meet the following criteria to be enrolled in the study:

1. Licensed primary care provider (PCP) (MD, DO, NP, PA) currently

|             |                                                                                                                                                |                       |
|-------------|------------------------------------------------------------------------------------------------------------------------------------------------|-----------------------|
|             | Clinical Study Protocol                                                                                                                 |                       |
|             | Title: Measuring the Clinical Utility of Aegis's Chronic Disease Management Test among VillageMD Providers: A CPV® Randomized Controlled Trial |                       |
| Supersedes: | Document Number:                                                                                                                               |                       |
|             | Effective Date:                                                                                                                                | Page: 18 of 25 |

practicing in the following areas:

- a) Internal medicine
- b) Family medicine
2. Have practiced as a PCP in internal or family medicine for greater than 2 but less than 30 years
3. Community / non-academic based practice setting
4.  $\geq 40$  patients under care weekly
5. Commonly treats patients with atrial fibrillation, coronary artery disease, congestive heart failure, diabetes, hypertension, COPD, and hyperlipidemia
6. Practicing in the U.S.
7. English-speaking
8. Access to the internet
9. Informed and voluntarily consented to be in the study

b. Subject Screening and Enrollment

Primary care provider participants will be contacted via an inclusive roster provided by VillageMD's leadership. Providers will include physicians, nurse practitioners and physician assistants. Potential participants will be contacted by email using a recruitment letter inviting them to participate. Participation is voluntary. All participants will be provided fair-market honoraria for their time.

We will maintain provider privacy and confidentiality in accordance with standard ethical practice. Informed consent will be obtained by having providers read the consent form and provide their acceptance via an online voluntary consent process where users indicate their agreement to participate at the time they are enrolled. We believe the voluntary consent process is sufficient for this study given the scientific sophistication of the study population and the very low risks of participation.

Providers will be considered enrolled into the study once informed consent is obtained.

c. Subject Withdrawal

If a participant fails to complete 3 CPV® vignettes per round, they will be withdrawn from the study and replaced with another provider. Any CPVs® from withdrawn subjects will be excluded from the analysis.

i. Withdrawal Criteria

Reasons for study withdrawal may include but are not limited to:

- Non-compliance with study procedures.
- Provider's right to withdraw consent at any time during the study with or without stated reason.

|             |                                                                                                                                                |                       |
|-------------|------------------------------------------------------------------------------------------------------------------------------------------------|-----------------------|
|             | Clinical Study Protocol                                                                                                                 |                       |
|             | Title: Measuring the Clinical Utility of Aegis's Chronic Disease Management Test among VillageMD Providers: A CPV® Randomized Controlled Trial |                       |
| Supersedes: | Document Number:                                                                                                                               |                       |
|             | Effective Date:                                                                                                                                | Page: 19 of 25 |

- ii. Documentation of Withdrawal of Subjects  
The reason for withdrawal of any provider from the study will be appropriately documented.

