## Study Design

The study is a prospective randomized cohort two-arm trial with six steps:

- 1) Enrollment: The study will enroll an estimated 166 practicing primary care providers, who practice at VillageMD clinics. An eligibility screener will be used to screen for eligibility (attached as Appendix A).
- 2) Provider survey: Once providers are enrolled in the study, they will be asked to complete an item questionnaire describing their practice, professional background and confidence in treating patients with cardiometabolic conditions.
- 3) Randomization: The 166 VillageMD providers will be randomized into two equally- sized arms: control group and intervention group.
- 4) CPVs® (First Round): Providers in both groups will complete three CPV® patient vignettes. Cases will be identical across the intervention and control arms. Cases are interactive and are presented on an online platform that is accessible via unique weblinks and any internet-connected computer.
- 5) Intervention education: For the intervention group, providers will receive educational materials describing the clinical validation and use cases of the Chronic Disease Management Test. The education materials are an orientation to the test, its use, the results directed to the participants that will adopt the CDMT (e.g., introduction slide deck, fact sheet, and/or case studies)
- 6) CPVs® (Second Round): All participating providers will then be asked to complete three additional CPV® patient simulations. The cases are again given to the doctors in a random order.

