## Sample Size

The study will recruit 166 providers (83 per arm), with an expected sample size of 75 participants in each arm accounting for an estimated 10% attrition.

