## 9. ADMINISTRATIVE CONSIDERATIONS

- a. Study Compliance  
The study will be conducted in compliance with this protocol, principles of ICH-E6, GCP and the Declaration of Helsinki and all applicable national regulations governing clinical trials.
- b. Protected Subject Information  
A copy of the IRB approved informed consent may be audited. The investigator or designee **must** explain to each subject the purpose and nature of the study, the study procedures, the possible adverse effects and all other elements of consent as defined in 21CFR §50. In accordance to individual local and national subject privacy regulations, the investigator or designee **must** explain to each subject prior to screening that for the evaluation of study results, the subject’s protected information obtained during the study may be shared with QURE Healthcare and its designees, regulatory agencies and IECs/IRBs. QURE Healthcare and Aegis will not use the subject’s protected information or disclose it to a third party without applicable subject authorization. It is the investigator’s or designee’s responsibility to obtain a written permission to use protected information from each subject. Any data collected from a subject prior to withdrawal will not be used in the analysis of study results.

|             |                                                                                                                                                |                       |
|-------------|------------------------------------------------------------------------------------------------------------------------------------------------|-----------------------|
|             | Clinical Study Protocol                                                                                                                 |                       |
|             | Title: Measuring the Clinical Utility of Aegis's Chronic Disease Management Test among VillageMD Providers: A CPV® Randomized Controlled Trial |                       |
| Supersedes: | Document Number:                                                                                                                               |                       |
|             | Effective Date:                                                                                                                                | Page: 24 of 25 |

c. Retention of Records

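### Providers who miss a vignette after randomisation are replaced and wholly excluded, so the analysis set depends on post-allocation behaviour and the rule does not fit the 10% attrition allowance

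*Protocol*

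**What the plan says.** The Study Design part of the synopsis lists six steps. At step 3 the providers "will be randomized into two equally- sized arms: control group and intervention group". Round 1 of the vignettes is step 4, the education of the intervention arm is step 5, and round 2 is step 6.

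Section 4.c (Subject Withdrawal) then sets the rule for providers who do not finish three vignettes in a round: "they will be withdrawn from the study and replaced with another provider. Any CPVs® from withdrawn subjects will be excluded from the analysis". The listed reasons for withdrawal also include non-compliance with study procedures. Section 9.b (Protected Subject Information) states the exclusion a second time: "Any data collected from a subject prior to withdrawal will not be used in the analysis of study results".

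The Sample Size section of the synopsis plans for losses without mentioning replacement. It recruits 166, or 83 per arm, "with an expected sample size of 75 participants in each arm accounting for an estimated 10% attrition".

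The main analysis, in the synopsis under Data Analysis and in Section 8.b, is a between-arm difference-in-difference regression of vignette scores. Variation at baseline across all participants is an outcome in Section 3.1, and Section 8.b lists baseline variation among the primary outcome variables.

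**The concern.** A provider can fail the completion rule only after being allocated. The rule therefore compares completers with completers, not the groups that randomisation made alike. If the reasons for stopping differ between arms and relate to the outcome, the arms are no longer comparable. A difference in completion is plausible because only intervention providers have educational material to work through between rounds.

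Two further consequences follow from the text. A provider who finishes round 1 and misses one round 2 vignette loses three valid baseline vignettes, although baseline variation is a stated outcome. And the protocol describes two incompatible ways of dealing with losses: accept them (83 falls to 75), or refill every vacancy.

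**Working it through.** **1. The protocol's own sample-size figure.** Inputs from Sample Size: 83 per arm, 10% attrition, 75 expected.
- Forward: 83 × 0.90 = 74.7, which rounds to 75.
- Backward: 75 / 0.90 = 83.3 per arm; 150 / 0.90 = 166.7 in total.

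The figure reproduces to within rounding, and it describes a trial without replacement.

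**2. The same figure under Section 4.c.** If each non-completer is replaced until the place is filled, 83 per arm (166) complete. With 10% loss, also among replacements, recruitment is 166 / 0.90 = 184.4, so about 185.

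| Rule | Recruited | Completers |
|---|---|---|
| Sample Size section | 166 | about 150 (75 per arm) |
| Section 4.c as written | about 185 | 166 (83 per arm) |

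**3. What selection could do to the effect estimate.** The protocol gives no SD, no correlation between rounds and no loss by arm, so this is an illustration on assumptions. Let provider scores in each round be normal with SD 1 and correlation ρ between rounds, with no true effect. Let the lowest 10% on some quantity leave the intervention arm and nobody leave control. Removing the lowest 10% shifts the mean of that quantity by φ(1.2816)/0.9 = 0.195 of its own SD.

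The planned contrast is the change, round 2 minus round 1, whose SD is √(2(1−ρ)). Taking 75 per arm, its standard error is √(2/75) × √(2(1−ρ)) = 0.163 × √(2(1−ρ)). The bias depends on what drives dropout:
- Stable overall level (mean of both rounds): uncorrelated with change, so bias 0.
- Round 1 score: −0.195(1−ρ).
- Round 2 score: +0.195(1−ρ).
- The provider's own change: +0.195 × √(2(1−ρ)).

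| ρ | Level | Round 1 score | Round 2 score | Own change | SE |
|---|---|---|---|---|---|
| 0 | 0 | −0.195 | +0.195 | +0.276 | 0.231 |
| 0.5 | 0 | −0.097 | +0.097 | +0.195 | 0.163 |
| 0.7 | 0 | −0.058 | +0.058 | +0.151 | 0.126 |

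Dropout driven by either round's score biases the estimate by at most 0.195/0.231 = 0.84 of a standard error (at ρ = 0), and less as ρ rises. Only dropout driven directly by each provider's own change exceeds one standard error, at 0.195/0.163 = 1.2 times for every ρ.

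A milder case: losses of 15% against 5%, with non-completers' change 0.5 SD lower. The bias is (0.15 − 0.05) × 0.5 = 0.05 SD, or 0.05/0.163 = 0.31 of a standard error at ρ = 0.5. If dropout is equal in both arms and unrelated to outcome, the bias is zero.

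**4. Baseline outcome.** This needs no assumption. Sections 4.c and 9.b remove round 1 vignettes that were completed before the provider failed the rule, while Section 3.1 defines baseline variation over all participants.

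**The case against.** The strongest reply is that the planned analysis already guards against the obvious form of selection. Because the rule keeps only providers with both rounds, losing providers who score low throughout shifts both rounds alike and cancels. That stands, and it limits the point. It does not cover selection on one round's score or on response to the intervention.

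It is also fair that nothing shows the education step drives people out. It is a slide deck, webinar, fact sheet or case studies, and participants are paid. So arm-dependent completion is a possibility, not a finding.

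On sample size, the Study Design text calls 166 an estimate, and one could imagine that 166 already counts replacements for a target of 150 completers (150 / 0.90 = 166.7). The protocol does not say so. It randomises all 166 into two equal arms, and the replacement rule carries no cap. The passages still need reconciling.

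A later SAP might add an analysis of all randomised providers. It would, however, have to override an exclusion stated twice in the protocol, so this is not detail merely left for later.

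Finally, retaining everyone gains less than it may seem. A provider with no round 2 vignette has no post-intervention outcome and adds little to the effect estimate. The gain there comes mainly from providers with one or two round 2 vignettes. The baseline outcome gains from everyone with round 1 data.

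**Conclusion.** The concern holds as a fault in how the analysis set is defined and in how the sample-size text fits the withdrawal rule. The order of events, the exclusion and the replacement are explicit. The mismatch is 150 against 166 completers, and 166 against about 185 recruited, assuming the protocol's own 10% loss.

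The bias cannot be sized from the document. The figures in step 3 rest on normal scores, equal variances, one-sided loss and an assumed ρ.

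Some stronger readings are tempting but unsupported:
- That the rule favours the test. The sign reverses if providers with low round 1 scores leave the intervention arm.
- That a 0.195 SD shift outweighs a standard error of 0.163 SD. Those figures belong to a single-round comparison of means, not to the planned contrast.
- That withdrawn providers' data are destroyed. The text only keeps them out of the analysis.
- That replacements fall outside the random sequence. The protocol does not say how they are allocated.

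**What to change.** - In Sections 4.c and 9.b, delete the replacement and exclusion rules, except where a provider withdraws consent for use of the data.
- State that all randomised providers are analysed in their assigned arm, using every completed vignette, in a mixed model that accepts incomplete rounds. Keep completers-only as a sensitivity analysis.
- Report completion by arm and by round.
- Keep the Sample Size text as it is: 166 recruited with a 10% allowance.

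The cost is mainly wording. Section 9.b sits among the privacy and consent provisions, so any matching commitment to participants would have to be checked and may need revising. The model also moves away from the fixed-effects form named in the synopsis, and it relies on missing-at-random for incomplete rounds. The change is best made before any provider is excluded or replaced.

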## 5. TREATMENT OF SUBJECTS

The subjects are primary care providers, presenting minimal risk to participation that is likely no different from the probability and magnitude of physical or psychological harm that is normally encountered in the daily lives. Possible risk would be loss of confidentiality and revelation of their case results, which will only be available to study administrators. Participants (providers) will be informed of these risks and asked to provide consent before participation. Participation is strictly voluntary. Subjects will be appropriately compensated for their time participating in the study.

## 6. STUDY PROCEDURES

At enrollment, each eligible provider who agrees to participate will be assigned a unique subject identification number for internal tracking of completion and data collection. Only the study team will have access to the subject's identity. The subject's name or other identifying information will not be used in analysis or reporting. The main study procedures or assessments will include but are not limited to: collection of demographic and practice information during the screening process and completion of CPV® cases.

### 6.1 Pre-Screening and Eligibility

The evaluations for inclusion and exclusion criteria will include professional licensure and clinical volume, as described in Section 4 above.

### 6.2 Completion of Questionnaire

Enrolled providers will then be asked to complete a questionnaire describing their practice and professional background. The questionnaire will consist of 10-15 questions to better understand provider demographics, training and practice environment. It will be administered immediately upon enrollment into the study.

### 6.3 Completion of CPV® cases

CPV® cases will be designed to simulate typical patients with chronic cardiometabolic conditions and polypharmacy presenting in clinical situations. In each case, providers will answer questions about their preferred course of action to work-up, assess, and manage patients. Intervention group providers only will also receive educational materials upon the CDMT prior to their CPV® cases, and during their post-intervention CPV® cases, will receive CDMT results at the appropriate point in each round 2 CPV® case whether they select it or not.

|             |                                                                                                                                                |                       |
|-------------|------------------------------------------------------------------------------------------------------------------------------------------------|-----------------------|
|             | Clinical Study Protocol                                                                                                                 |                       |
|             | Title: Measuring the Clinical Utility of Aegis’s Chronic Disease Management Test among VillageMD Providers: A CPV® Randomized Controlled Trial |                       |
| Supersedes: | Document Number:                                                                                                                               |                       |
|             | Effective Date:                                                                                                                                | Page: 20 of 25 |

## 7. STUDY DATA COLLECTION

Data entry and resolution will be performed in real-time concurrent with CPV® data collection. All data will be linked to providers via a unique identification number; only the study team will have access to their identities. Electronic data files will be password protected. Periodic audits will ensure data protection procedures are being followed. No providers will be mentioned by name in any data output.

## 8. STATISTICAL ANALYSIS

### a. Study Hypotheses

1. Provider participants at baseline will not recognize that patients do not meet therapeutic goals due to medication non-adherence and show high levels of unwarranted variation in their work-up, recognition, and management of medication non-adherence in patients with more than one chronic cardiometabolic conditions and associated polypharmacy using in the CPV® patient simulations.
2. Providers will not recognize that patients do not meet therapeutic goals due to DDI and show high levels of unwarranted variation in their work-up, recognition, and management of medication non-adherence in patients with more than one chronic cardiometabolic conditions and associated polypharmacy using in the CPV® patient simulations.
3. The intervention group, those who receive educational materials about the CDMT and CDMT results in their round 2 patient, will improve their quality of care and have less practice variation when caring for their CPV® patients with more than one chronic cardiometabolic conditions and associated polypharmacy, as measured by management decisions to recognize and/or manage medication non-adherence, DDI, and associated co-morbidities.
4. The additional information from the CDMT will result in better distinction between medication non-adherence and DDI and lead to better overall care including reduction in over-use of invasive diagnostic work-up and treatment, and a reduction in cost in a subset of patients. The associated cost savings, particularly for those patients will come from obviating high-cost workup, avoidance of unneeded subspecialty referrals, increased diagnosis and treatment of drug-drug interactions and/or reducing the frequency or number of medical interventions ordered.
5. Of the nine simulated cases that will focus on patients with multiple chronic cardiometabolic conditions and polypharmacy, there will be a subset of use cases where the CDMT demonstrates greater utility.
6. Providers with access to the education materials and CDMT will diagnose

|             |                                                                                                                                                |                       |
|-------------|------------------------------------------------------------------------------------------------------------------------------------------------|-----------------------|
|             | Clinical Study Protocol                                                                                                                 |                       |
|             | Title: Measuring the Clinical Utility of Aegis’s Chronic Disease Management Test among VillageMD Providers: A CPV® Randomized Controlled Trial |                       |
| Supersedes: | Document Number:                                                                                                                               |                       |
|             | Effective Date:                                                                                                                                | Page: 21 of 25 |

medication non-adherence and potentially harmful DDIs more often than control providers.

